## Abstract

**Background:**

Genital *Chlamydia trachomatis* infection is a major public health problem worldwide affecting mostly youth. Sweden introduced an opportunistic screening approach in 1982 accompanied by treatment, partner notification and case reporting. After an initial decline in infection rate till the mid-90s, the number of reported cases has increased over the last two decades and has now stabilized at a high level of 37,000 reported cases in Sweden per year (85% of cases in youth). Sexual risk-taking among youth is also reported to have significantly increased over the last 20 years. Mobile health (mHealth) interventions could be particularly suitable for youth and sexual health promotion as the intervention is delivered in a familiar and discrete way to a tech savvy at-risk population. This paper presents a protocol for a randomized trial to study the effect of an interactive mHealth application (app) on condom use among the youth of Stockholm.

**Methods:**

446 youth resident in Stockholm, will be recruited in this two arm parallel group individually randomized trial. Recruitment will be from Youth Health Clinics or via the trial website. Participants will be randomized to receive either the intervention (which comprises an interactive app on safe sexual health that will be installed on their smart phones) or a control group (standard of care). Youth will be followed up for 6 months, with questionnaire responses submitted periodically via the app. Self-reported condom use over 6 months will be the primary outcome. Secondary outcomes will include presence of an infection, Chlamydia tests during the study period and proxy markers of safe sex. Analysis is by intention to treat.

**Discussion:**

This trial exploits the high mobile phone usage among youth to provide a phone app intervention in the area of sexual health. If successful, the results will have implications for health service delivery and health promotion among the youth. From a methodological perspective, this trial is expected to provide information on the strength and challenges of implementing a partially app (internet) based trial in this context.

**Trial registration:**

ISRCTN 13212899, date of registration June 22, 2017.

## Background

*Chlamydia trachomatis (C.trachomatis)* and other sexually transmitted infections (STIs) are considered a major public health problem worldwide affecting mostly youth [1]. The World Health Organisation estimates that 357 million new infections with one of four STIs: Chlamydia, gonorrhoea, syphilis and trichomoniasis occur each year [1]. *C.trachomatis* is the most commonly reported STI worldwide. If untreated, *C.trachomatis,* as well as some other bacterial infections, could lead to adverse reproductive health outcomes such as infertility [2]. *C.trachomatis* also increases susceptibility to HIV infection [3]. In addition, drug resistance, is a major threat to reducing the impact of STIs worldwide [1].

An objective comparison of *C.trachomatis* prevalence between countries is difficult as reporting procedures and national screening practices vary widely [4]. There are large differences in *C.trachomatis* control policies across Europe and worldwide. Sweden, Denmark, UK are all examples of countries with well-functioning screening programs [5].

### C.Trachomatis in Sweden

Sweden has a long tradition of testing. An opportunistic screening approach was introduced already in 1982 offering *C.trachomatis* testing to women requesting contraceptives, antenatal care or abortion, male partners of infected women were also tested (contact tracing) [6, 7]. Then, in the late 80s the infectious disease law was changed and came to include free testing and treatment of *C.trachomatis*, partner notification and case reporting [8]. The incidence of *C.trachomatis* and its sequelae decreased up until the mid-1990s [6, 7, 9]. The Swedish screening program was held up as an example of success in bringing down *C.trachomatis* infection rates [10].

Despite this initial positive effect of widespread testing, and despite significant efforts, including increasing availability of testing and treatment services, the incidence of *C.trachomatis* in Sweden has, over the past two decades, steadily increased and has now stabilized at a high level of approximately 37,000 reported cases per year. Youth aged 15–29 constitute the majority (85%) of all cases [11].

The high rates of *C.trachomatis* infection, notwithstanding the resources and efforts invested, caught the attention of several stakeholders in Sweden. A National Plan for Chlamydia Prevention was launched in 2009. This resulted in initiatives to increase condom use, improve knowledge about *C.trachomatis* infection and the consequences of unprotected sex, i.e. focusing on primary prevention strategies, but also increase the availability of testing and treatment services for infection i.e. secondary prevention strategies [12].

### Sexual behavior of youth in Sweden

As a response to the increasing level of *C.trachomatis* in the country, young people’s sexual habits have been surveyed in studies in Sweden [13–15]. Sexual risk-taking among youth has significantly increased over the last 20 years, especially among young women [16]. Although knowledge and confidence in condoms as an effective way of prevention of STI has increased over the last decades, this has not resulted in more widespread use [17]. In a large national population based study, 50% of women and 40% of men between the ages of 18 and 30 stated that they never or seldom used condoms with a temporary partner [14]. In a national survey with 15,000 youth aged 15–29, about 70% reported not using a condom at the last intercourse and 50% said they did not use a condom with a new partner at the last intercourse [13].

Many studies have focused on finding and evaluating how to best tailor effective sexual health interventions [18–20]. The effects of interventions vary. Educational interventions show positive results in terms of increased knowledge regarding STI and condom use, and even in attitude changes [21]. However, increased knowledge about STI does not necessarily translate into a positive impact on behavior (increased condom use, reduction in sexual partners) [22]. A motivational behavioural intervention was evaluated in a large randomised study in US, but the intervention did not have any effect on condom use [23]. Motivational Interview (MI) as a method to change sexual risk behaviour has shown mixed effectiveness in Sweden [24, 25]. With increasing demands of availability and increasing number of *C.trachomatis* tests being performed, it can be argued that scaling up of successful MI techniques and other forms of face-to-face counseling are time consuming, and may not be feasible for already time-constrained staff to implement. Thus, there is an urgent need for new innovative ideas to promote safe sex among young people.

### mHealth interventions to promote safe sexual practices

Mobile health – mHealth is an increasingly popular way to deliver health promotive information to large parts of the public at low cost and serve as a complement to ongoing activities within the health care system. mHealth interventions could be particularly suitable for youth and sexual health promotion as the intervention is delivered in a familiar and discrete way to a tech savvy at-risk population [26]. mHealth also offers the possibility of a range of different interventions for example reminder (to use a condom or to test), and motivational messages, peer feedback – each of which allows differing levels of engagement [27]. Furthermore creative mHealth interventions such as games, videos, and challenges (quizzes, puzzles etc) could engage youth in sexual health awareness and behavioral change readiness. The coverage of mobile phone ownership among young people in Stockholm County is high. Among the population in Sweden 97% own a mobile phone and the majority of these are smart phones [28].

A systematic review of randomized controlled trials (RCTs) of sexual health interventions delivered by mobile technologies was recently published [27]. While there is promising evidence of the impact of mHealth on increased knowledge about STI, and increased levels of testing for STI, there is still a need for better developed interventions that are more engaging and aimed at behavioral changes i.e. increased condom use. Given the high use of mobile phones among the youth of Stockholm, and the high rates of *C.trachomatis* in this group, a well-designed mHealth intervention merits testing here. Furthermore, there has been no previous evidence from Sweden on the use of mHealth interventions to promote safe sexual practices among the youth. If the interventions can increase condom use and decrease the occurrence of *C.trachomatis* this will have implications in terms of supporting the opportunistic screening program by complementing its preventive arm. This could reduce costs for the healthcare system; testing and treatment are costly, more so, there are some indications of antibiotic use lead to resistance among *C.trachomatis* [29]. Such an intervention could be potentially delivered to youth across wide geographic areas at low cost.

### Objective

The aim of this pragmatic randomized trial is to compare the effectiveness of a mobile phone application to improve sexual health among youth of Stockholm County to routine care. Safe sexual practices will include self-reported condom use (primary) and *C.trachomatis* positivity (secondary).

## Methods

This study is a multicentre (8 recruiting clinics), parallel group randomised controlled trial. Eligible participants are randomised in a 1:1 allocation ratio to one of two arms: an intervention arm, in which youth receive the interactive application (app) called the ‘Skyddslaget’ or ‘protection team’ app in addition to the standard of care (defined below); and a control arm in which they receive only the standard of care Fig. 1.

**Fig. 1 Fig1:**
[figure not shown]
Flow diagram

### Study setting

The settings for this trial are the Youth Health Clinics (YHC) in Stockholm County. These youth clinics are part of nationwide network of such clinics in Sweden. The target age of clients attending the YHC ranges from 12 to 23 years old. Besides contraceptive counselling services and the provision of contraceptives to youth, the clinics are involved both in primary prevention of STI, i.e. sexual education to school classes, and secondary prevention i.e. testing, contact tracing and treatment services. Condoms are distributed for free at the YHC. The YHCs therefore provide a ‘one stop shop’ service with regard to sexual health for young people. Each clinic is staffed by nurses/midwives, behavioural therapists, social workers and a physician. In the whole country there are approximately 250 clinics, and in Stockholm County there are 33 YHC. The trial will be conducted at 8 of 33 YHC in Stockholm County.

### Inclusion and exclusion criteria

All youth over 18 years old who visit any of the eight YHCs in Stockholm, as well as all youth between the ages of 18–23 years old who register interest to participate via the trial website, will be potential participants for the trial if they also meet other inclusion criteria. Youth included in the trial should (a) own a smart phone and (b) should have had at least two sexual partners during the previous 6 months. This second criteria is to ensure youth included in the trial have recently had sex outside a stable relationship. Youth who fulfil the inclusion criteria but do not wish to participate will be excluded from the trial. Women who have sex with women will be excluded from the trial as the intervention focuses on condom use.

### Recruitment

Youth who attend any of the eight YHC and who fulfil the inclusion criteria will be informed about the study and asked about willingness to participate. In order to facilitate the recruitment process and identify eligible participants, midwives at each of the study sites will be carefully informed about the study. At time of the recruitment a member of the research team or the midwife will provide information to youth who show interest in participating in the trial.

Youth can also register interest in participating in the trial via the trial website (www.skyddslaget.se). These potential participants will be contacted by the research team. Those who fulfil the inclusion criteria will meet a member of the research team who will provide information about the trial.

### Informed consent

All eligible youth who express an interest will individually be given an initial verbal description of the proposed study by a trained member of staff. They will then be presented a written informed consent form in Swedish.

### Randomization

Stratified randomization, separately for male and female participants, will be performed. Within each stratum, block randomization will be used to ensure balanced representation in the two treatment arms (control and intervention) as recruitment progresses. Blocks of 4 and 6 will be used. Randomisation will be done electronically by an interactive web response system at the time of recruitment. Once participants have consented, each participant will be given a study identification number at the site and instructed in the protocols based on their randomisation group. This will allow allocation concealment at the sites.

### Intervention

The intervention which will be evaluated in this trial will consist of “Skyddslaget” app, a mobile phone app to promote safe sex among the youth. This intervention will be compared against standard of care.

### Description of intervention

This smart phone application was developed based on individual interviews, focus group discussions with youth in Stockholm, and considering health behavior change principles.

The intervention will be in the form of a smart phone application, the “Skyddslaget” app, which will be installed onto smartphones of those applicants allocated to the intervention arm of the trial. The app is intended to deliver ‘safe-sex and STI’ relevant snippets of information (facts) to participants on their phones in a youth friendly format. In addition it will also have a more interactive and engaging element which will include weekly challenges (games) and quiz, as well as personal stories related to safe sex narrated by peers. Activities/information snippets within the app will be dynamic, i.e. change periodically over time. The intervention will run over a period of 6 months from enrolment into the study.

### Description of the control

The participants in the control arm will also receive an app, which will be a dummy application that will be downloaded onto their phones. This app will not provide an information or have any interactive modules but will only contain only the study baseline and follow-up questionnaires.

### Standard of care

Both the control and intervention groups will receive the standard of care which is as follows:

Guided by national laws and regulations, regional policies control the preventive work in the different County Councils in Sweden [30]. Standard of care for youth visiting the YHCs in Stockholm County includes exploring sexual behaviour of the individual, give recommendations and prescription of contraceptives, information about and distribution of condoms, testing for STI upon request from the youth and/or upon recommendation from the staff. If the STI test is positive the youth is called back to the clinic for treatment and contact tracing. A test of cure and/or re-testing after a positive test is not routinely recommended. The standard operating procedures (SOP) might differ between different YHCs.

Participants recruited outside the clinics (via the trial website) will be receive the standard of care as above should they choose to visit the YHC.

### Outcome measures

### Primary outcome

Self-reported condom use during the past 6 months.

### Secondary outcomes

Number of partners during the study period. Number of tests for *C. trachomatis* during the study period. Occurrence of pregnancy during study period occurrence of STI during the study period.

### Outcome assessment

Primary outcome: self-reported condom use (number of sexual partners when condom was always used/total number of sexual partners in percentage) during the past 6 months. This 6 months measure will be computed by summing of data provided at 3 months and 6 months after enrollment. (Each measure will refer to the previous 3 months).

Secondary outcomes: Self-reported number of partners (mean); number of STI test (mean); occurrence of STI (yes/no); and occurrence of pregnancy (yes/no) during the study period will be assessed at 6 months.

For self-reported number of partners, the mean number of partners per 3 month period will be calculated. This will be based on the average of data provided at the 3 months and 6 months assessment questionnaires. (Each measure will refer to the previous 3 months). For the other two secondary outcomes, a ‘yes’ response at any point in the study will be considered.

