### Study procedures: Data collection and follow ups

There are no in person follow ups intended in this study, though the patient will be informed that s/he can contact the research team/study clinic at any point during the study. Data will be collected at three time points – at baseline, at month 3 and month 6. All data will be sent in by participants via the app. Appropriate security measures to ensure safe and confidential transfer of data onto a safe haven server have been made.

The trial team will make efforts to ensure that participants respond to the data requests at month 3 and 6. Youth often lead a life full of variety in terms of living arrangements and relationship status. In addition, smart phones might break, be lost, and phone numbers might be changed. Therefore, obtaining data at the required time points could prove a challenge. Participants will consent to a research assistant contacting them, if responses via the app are not received. Three attempts at contact will be made within 10 days of the expected date of receipt. If the participant is not traced/does not respond during this time, he/she will be considered lost to follow up.

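### Self-reported STI occurrence depends on who gets tested: if testing differs between arms, the comparison can dilute, hide or reverse a benefit

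*Protocol article*

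**What the plan says.** All places are in the protocol article.

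- **Scale and scoring.** Outcome assessment lists, side by side, "number of STI test (mean); occurrence of STI (yes/no" among the self-reported secondary outcomes. For the yes/no outcomes, which are STI and pregnancy, a yes "response at any point in the study will be considered". There is no third level.
- **How a test comes about.** Standard of care, given to both arms, includes "testing for STI upon request from the youth and/or upon recommendation from the staff". Website recruits receive that care only "should they choose to visit the YHC". No study test is described at entry, 3 months or 6 months.
- **Follow-up.** Study procedures states: "There are no in person follow ups intended in this study". All data are submitted by participants through the app.
- **Expected effect on testing.** The background section on mHealth reports promising evidence, from a systematic review of randomised trials, of "increased levels of testing for STI".
- **Role of the outcome.** The Objective names *C. trachomatis* positivity as the secondary measure of safe sexual practice, without a denominator.
- **Missing data.** Statistical analysis imputes missing values under a missing-at-random assumption and promises sensitivity analyses without naming one for testing.

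The article does not say how a participant who was never tested is coded.

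**The concern.** A participant can report an infection only if it was diagnosed, and diagnosis normally needs a test that the participant sought or accepted. Someone with an undiagnosed infection will answer no. That is a valid answer on a two-level item, so imputation of missing values does not touch it. The yes/no rate therefore measures infection and testing together.

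This would matter little if both arms were sure to test equally. The trial, however, treats testing as something the intervention might change: it is a secondary outcome, and the cited evidence points upward. If the app succeeds on testing, it finds more of the infections present in its own arm, and the STI comparison moves against it. At stake is the secondary outcome that the Objective names, and any statement that the app lowers, or fails to lower, infection.

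**Working it through.** **The plan's own figure.** The article gives no number for the STI outcome. Its only calculated size is for condom use, used here just to fix the arm sizes. With 50% vs 70%, two-sided α 0.05 and 90% power:

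- n′ = [1.960·√(2·0.6·0.4) + 1.2816·√(0.25 + 0.21)]² / 0.2² = 124 per arm.
- With continuity correction, n = (124/4)·[1 + √(1 + 4/(124·0.2))]² = 133.8, so 134 per arm and 268 in total, as stated.
- 268/0.6 = 446.7, against the stated 446 (223 per arm).

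**Model.** Let r be the risk of infection over the study and t the proportion tested. Assume that risk is the same in tested and untested people, that a test finds the infection, and that an undiagnosed infection is reported as no. Then:

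- observed rate = r × t
- observed RR = true RR × (t app / t control)

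**Inputs.** The documents give neither r nor t. All values below are assumptions for illustration.

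**No true effect.**

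- r = 10% in both arms, t = 40% vs 60%: 0.40 × 0.10 = 4.0% and 0.60 × 0.10 = 6.0%. Observed RR = 1.50.
- t = 30–50% in control and 40–70% with the app, in 10-point steps with the app higher: the smallest ratio is 60/50 = 1.20 and the largest 70/30 = 2.33. These ratios do not depend on r.

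**With a true benefit, t = 40% vs 60% (ratio 1.5).**

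| True RR | Observed RR | Reading |
|---|---|---|
| 0.80 | 1.20 | reversed |
| 0.67 | 1.00 | hidden |
| 0.60 | 0.90 | diluted |

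The break-even true RR is t control / t app: 0.40/0.60 = 0.67 here, and 0.43 (30/70) to 0.83 (50/60) over the grid. A smaller testing gap does less harm: at 40% vs 50%, a true RR of 0.60 reads 0.60 × 1.25 = 0.75.

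**If risk is not equal.** Keep no true effect and 40% vs 60% tested, with 10% risk among the 40% who would test anyway. If the extra 20% tested in the app arm have 5% risk, its rate is 0.40 × 0.10 + 0.20 × 0.05 = 5.0%, RR 1.25. If they have 15% risk, it is 0.04 + 0.03 = 7.0%, RR 1.75.

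**Chance of a spurious significant increase.** For 4.0% vs 6.0%, normal approximation, SE = √(2·0.05·0.95/n):

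- n = 134: SE 0.0266, 0.02/SE = 0.751, Φ(0.751 − 1.960) = 11%.
- n = 223: SE 0.0206, 0.02/SE = 0.969, Φ(0.969 − 1.960) = 16%.

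The nominal value in that direction is 2.5%. With about 134 × 0.04 = 5 and 134 × 0.06 = 8 events expected, these are rough figures.

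**What the recording of the untested contributes.** In the same example, giving the untested the risk of the tested yields 0.40 × 0.10 + 0.60 × 0.10 = 10% in control and 0.60 × 0.10 + 0.40 × 0.10 = 10% with the app, RR 1.0. The whole of the 1.5 comes from treating unknown status as no.

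**The case against.** Several counter-arguments have weight.

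- **The coding is not written down.** A reader might infer that the protocol counts untested participants as no. It does not say so; the scoring rule says only what a yes does, and it covers pregnancy too. The handling of never-tested participants may sit in an analysis plan that is not shown. This stands as to the text. It does not remove the point, because the article itself fixes a self-reported two-level item without a study test, and an undiagnosed infection has nowhere to go but no.
- **A testing difference is not built in.** A reader might infer that detection differs between arms by design. Both arms receive the same standard of care, the evidence cited concerns mHealth in general, and the description of this app lists facts, challenges, a quiz and peer stories but no prompt to test. A difference is plausible, not established.
- **The app need not look harmful.** A reader might infer that more testing will show up as more infection. A large enough true benefit still shows as a benefit, only smaller.
- **Samples taken at the recruiting visit.** A result pending at enrolment could be reported as a study infection. That is settled before allocation, so randomisation is expected to balance it. It may add noise but does not favour an arm.
- **Testing is already compared by arm.** This helps a reader notice a difference. But a mean number of tests is not the proportion tested, and nothing ties the STI result to it.

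**Conclusion.** The point holds as a conditional one. STI occurrence rests on self-initiated or staff-recommended testing and on self-report, so a difference in testing between arms would bias the comparison by roughly the ratio of the proportions tested. If the app raises testing, the bias runs against it.

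The size is unknown. The illustrative range of 1.2 to 2.3 rests on assumed testing proportions and on equal risk in tested and untested people; lower risk among the additionally tested would shrink it. The documents do not support saying that the app will appear to increase infection.

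The effect is confined to a secondary outcome, although one that the Objective names. The change is worth making because it costs almost nothing.

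**What to change.** 1. From the test counts already collected, report by arm, among all randomised participants, a three-level outcome: not tested / tested, all negative / tested, any positive. Show participants without follow-up data separately, so that not tested is not confused with lost. The test count and the STI answer must refer to the same infections: Secondary outcomes speaks of *C. trachomatis* tests, Outcome assessment of STI tests.
2. Add a sensitivity analysis that treats the infection status of never-tested participants as unknown, for example by varying their assumed risk from zero up to that of the tested.
3. State in advance that the yes/no rate will not be read as an effect on infection if testing differs between arms.

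The cost is analysis wording and one table. An item asking the sample date, to separate results from samples taken at or before enrolment, would be a minor optional refinement.

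Downside: positivity among the tested conditions on something that happens after randomisation, so it is supportive only. The sensitivity analysis in turn rests on an assumption about people who chose not to test that the data cannot check. These steps make the limit visible; they do not remove the bias.
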